## Abstract

**Background:**

Adoption of an active lifestyle plays an important role in the management of type 2 diabetes. Online interventions targeting lifestyle changes in adults with type 2 diabetes have provided mixed results. Previous research highlights the importance of creating theory-based interventions adapted to the population’s specific needs. The online intervention “MyPlan 2.0” targets physical activity and sedentary behavior in adults with type 2 diabetes. This intervention is grounded in the self-regulation framework and, by incorporating the feedback of users with type 2 diabetes, iteratively adapted to its target population.

**Objective:**

The aim of this paper is to thoroughly describe “MyPlan 2.0” and the study protocol that will be used to test the effectiveness of this intervention to alter patients’ levels of physical activity and sedentary behavior.

**Methods:**

A two-arm superiority randomized controlled trial will be performed. Physical activity and sedentary behavior will be measured using accelerometers and questionnaires. Furthermore, using questionnaires and diaries, patients’ stressors and personal determinants for change will be explored in depth. To evaluate the primary outcomes of the intervention, multilevel analyses will be conducted.

**Results:**

The randomized controlled trial started in January 2018. As participants can start at different moments, we aim to finish all testing by July 2019.

**Conclusions:**

This study will increase our understanding about whether and how a theory-based online intervention can help adults with type 2 diabetes increase their level of physical activity and decrease their sedentary time.

**International Registered Report Identifier (IRRID):**

DERR1-10.2196/12413

## Introduction

Diabetes is associated with various health problems including kidney failure, retinopathy, and cardiovascular disease [1]. By 2035, it is estimated that one in ten adults will have diabetes [1]. This exponential growth of diabetes is largely accounted for by type 2 diabetes, which is responsible for 85%-95% of the disease cases [1]. Adopting an active lifestyle (ie, being physically active and limiting sedentary behavior) has shown to play an important role in both the prevention and management of type 2 diabetes [2,3]. Consequently, cost-effective approaches that help adults with type 2 diabetes in increasing their physical activity and reducing their sedentary behavior are needed.

Electronic health (eHealth) and mobile health (mHealth) interventions have the potential to reach large populations in a cost-effective way and are effective in promoting an active lifestyle in the general population [4]. Nevertheless, research about the effectiveness of online interventions targeting adults with type 2 diabetes reveals mixed results [5-7]. Based on these findings, several proposals have been formulated to better design and implement eHealth and mHealth interventions for adults with type 2 diabetes. First, interventions should be grounded in and informed by theoretical models [5,7,8]. Research revealed that online programs that are developed using theoretical models result in larger effect sizes [9]. A useful perspective may well be the self-regulation framework, which focuses on both preintentional (such as increasing knowledge) and postintentional (such as action and coping planning) processes of behavior change [10]. This framework describes behavior change as a goal-guidance process starting from personal determinants for change until goal maintenance or, if necessary, disengagement [11]. Second, online interventions should take into account the perspective and needs of the users. This can be accomplished by involving end users during the entire developmental process of the online program [12,13]. Third, developers should address the high levels of attrition that are negatively affecting many online interventions [14]. Combining a website with a reminder system, such as automated emails or text messages, may be one of the ways to reinforce website use [7].

There are many papers discussing the effects of online interventions. Nevertheless, a clear and thorough description of the interventions themselves is often missing. This impedes research, as researchers often start from scratch when creating an intervention. The publication of study protocols that clearly describe the active ingredients and the “dose” of the interventions are therefore needed [5]. This study describes the protocol for a randomized controlled trial examining how a self-regulation–based eHealth and mHealth intervention (“MyPlan 2.0”) targeting sedentary behavior and physical activity influences the behavior-change process of adults with type 2 diabetes. The needs of adults with type 2 diabetes were taken into account, as they were actively involved in the development of the program [15,16]. “MyPlan 2.0” consists of a website that motivates users to create, follow, and maintain their own goals for physical activity or sedentary behavior in combination with an optional mobile app offering daily support. The aim of this paper is to describe “MyPlan 2.0” and provide the study protocol that will be used to investigate the website’s effectiveness and underlying mechanisms. The items addressed in this protocol paper are based on the 2013 Standard Protocol Items: Recommendations for Interventional Trials (SPIRIT) statement [17]. Multimedia Appendix 1 presents the completed SPIRIT checklist.

## Methods

### Ethical Approval

This study was approved by the Committee of Medical Ethics of the Ghent University Hospital (Belgian registration number: B670201732566) and registered as a clinical trial (Clinicaltrials.gov NCT03291171). Written informed consent from each participant will be obtained. Precautions will be taken to ensure participants’ privacy during data analysis.

### Study Design

A two-arm superiority randomized controlled trial will be performed. The study flow is depicted in Figure 1. Data will be collected during three home visits. During the first home visit, written informed consent will be obtained from the participants, and the participants will be asked whether they would like to increase their physical activity or decrease their sitting time. Participants will then complete questionnaires on physical activity, sedentary behavior, personal determinants for change (eg, self-efficacy), and health-related outcomes. Furthermore, participants’ weight and waist circumference will be assessed. Finally, participants from both groups will wear an accelerometer for a period of 10 days and fill out a morning and evening diary on each of these days. The diaries will assess participants’ daily goals and possible person-related barriers (ie, fatigue, stress, depressed mood, pain, nausea, and feelings of numbness or tingling in limbs).

After this period, LP will randomly allocate participants to the waiting list control group or the intervention group in a 1:2 allocation ratio by using an automated randomizer [18]. This will be done independent from patients’ choice to increase their physical activity or decrease their sitting time. Participants allocated to the intervention group who chose to increase their physical activity will be directed to the website targeting physical activity, whereas participants who chose to decrease their sitting times will be directed to the website targeting sedentary behavior. Participants owning a smartphone will be asked to download the mobile app. The website part of the intervention consists of five consecutive modules (a start module and four follow-up modules) spread over a 5-week period. Each week, participants from both groups will be phoned by a researcher. During these phone calls, questions regarding participants’ personal determinants for behavior change (eg, self-efficacy) will be repeated. In doing so, we will achieve the temporal separation needed to investigate causal pathways [19]. Furthermore, the phone calls will be used to check whether patients had hypoglycemia or made changes to their medication.

One week after completing the program (for the intervention group) or 6 weeks after finishing the baseline measures (for the control group), a second home visit will be scheduled during which the posttest will be carried out. In this phase, questions regarding process evaluation will be added to the questionnaires of the intervention group. Finally, 6 months after the baseline test, the intervention group will be visited a third time by the researchers to perform the follow-up test in order to examine whether the potential effects of the intervention are sustainable.

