### Hypotheses

Our primary hypotheses for this study are as follows: (1) The intervention group allocated to the module “Physical Activity” will show an increase in total physical activity from pre- to posttest compared to no change in the control group. This effect will be sustained in the intervention group from the posttest to the follow-up test. (2) The intervention group allocated to the module “Sedentary Behaviour” will show a decrease in sedentary behavior from pre- to posttest compared to no change in the control group. This effect will be sustained in the intervention group from the posttest to the follow-up test.

Our secondary hypotheses are as follows: (1) Positive changes in physical activity or sedentary behavior will be mediated by increases in the personal determinants self-efficacy, action planning, and coping planning. (2) The intervention group will have more positive health outcomes (ie, a lower weight; smaller waist circumference; and lower levels of fatigue, anxiety, and depression) from pre to follow-up test. (3) The negative effect of daily stressors (ie, fatigue, stress, depressed mood, pain, nausea, and feelings of numbness or tingling in limbs) on physical activity and sedentary behavior will be smaller in the intervention group from pre- to posttest compared to no change in the control group. This effect will be sustained in the intervention group from posttest to follow-up test.

As moderation analyses for online interventions targeting adults with type 2 diabetes are not usually performed [5], no hypotheses regarding the moderation effects are made. The following factors will be examined as potential moderators: age, sex, education, and chosen behavior (ie, physical activity or sedentary behavior).

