##### Personal Determinants

Personal determinants for behavior change (ie, self-efficacy, risk perceptions, outcome expectations, motivation, intention, action planning, coping planning, and self-monitoring) will be measured in both groups during each testing wave and the weekly phone calls. These determinants will be assessed using multiple items (minimum three items per determinant) that were selected by presenting a large number of items measuring Health Action Process Approach (HAPA) determinants to 11 experts in the self-regulation framework. All experts indicated whether each item measured the presented HAPA determinant and how sure they were of their answer [36]. Based on these responses, discriminant content validity was assessed using the method described by Johnston et al [36], and the best scoring items were selected. Each item has 10 answer options, ranging from “completely disagree” to “completely agree.”

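### Controls are not tested at 6 months, so secondary hypothesis 2 has no randomised comparison over its stated period and the 'sustained' clauses are uncontrolled within-arm comparisons

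*Protocol article*

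**What the plan says.** **Visits (Study Design).** For controls, "6 weeks after finishing the baseline measures (for the control group), a second home visit will be scheduled"; that is the posttest. The third visit, 6 months after baseline, is described for one arm only: "the intervention group will be visited a third time by the researchers to perform the follow-up test", and its purpose is "in order to examine whether the potential effects of the intervention are sustainable". No control visit after the posttest is described.

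**Hypotheses.** Each primary hypothesis has two parts. The first is a change "from pre- to posttest compared to no change in the control group". The second reads "This effect will be sustained in the intervention group from the posttest to the follow-up test". Secondary hypothesis 3, on daily stressors, has the same two-part form. Secondary hypothesis 2 differs: "The intervention group will have more positive health outcomes" (weight, waist circumference, fatigue, anxiety, depression), over the period from pretest to follow-up test, with no comparator named.

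**Sections that assume otherwise.** The sample-size paragraph under Participants enters two groups and three measurements. The Personal Determinants section says these items "will be measured in both groups during each testing wave and the weekly phone calls", and the questionnaire and accelerometry sections count three testing waves.

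**Table 3** lists weight, waist circumference and the three PROMIS scales at baseline, posttest and follow-up, without separating the arms.

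**The concern.** A claim that the intervention group does better on health outcomes is a claim against something. In a two-arm superiority trial that something is the randomised control arm, and at the endpoint of secondary hypothesis 2 that arm has no data. What remains is a before-after change in treated participants. It combines any intervention effect with time trend (including season), regression to the mean and the effect of repeated testing.

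The maintenance clauses raise a related problem. They predict that a gain will not be lost between posttest and follow-up, and they can be examined only in the intervention arm. The article gives no margin or criterion for calling an effect sustained. If a change that fails to reach significance were taken as maintenance, a small sample would favour that conclusion whether or not the effect had faded.

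At stake is how the 6-month findings can be described: as evidence from a randomised comparison, or as observation of one arm.

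**Working it through.** **1. Which hypothesis parts have control data**

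| Hypothesis part | Interval | Control data at both ends? |
|---|---|---|
| Primary 1 and 2, first part | pretest to posttest | yes |
| Primary 1 and 2, maintenance clause | posttest to follow-up | no |
| Secondary 2 | pretest to follow-up | no |
| Secondary 3, first part | pretest to posttest | yes |
| Secondary 3, maintenance clause | posttest to follow-up | no |

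The maintenance clauses say openly that they concern the intervention group. Secondary hypothesis 2 does not: it uses comparative wording for an interval in which a comparison cannot be made.

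**2. The stated sample size**

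Inputs from the Participants section: effect size 0.37, alpha .05, a beta of .90 (read as power .90), two groups, three measurements, N = 96 (64 + 32).

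Take 0.37 as the multivariate effect size f in a group-by-time test over three waves:
- df1 = 2, df2 = N − 3 = 93
- noncentrality = f² × N = 0.37² × 96 = 13.14
- power = .902 at N = 96 and .898 at N = 95

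So N = 96 is reproduced exactly, as a test that needs three waves in both groups. This may not be the route the authors took: half that value as f, with a correlation of about .22 to .25 that the article does not state, also gives 96 for three waves. The mismatch does not depend on the route, because three measurements in two groups are stated inputs and controls have only two.

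With the two shared waves and the same formula, N = 79 would suffice, and power at 96 would be .948. That changes the definition of the effect, so it is indicative only.

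**3. What a non-significant posttest-to-follow-up change would show**

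Assumptions, none given in the article: 0.37 is a difference in SD units, all 64 are analysed, the test is a two-sided paired t at .05, and the correlation rho between the two waves is .5 or .7.

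Standardised paired difference dz = loss / √(2(1 − rho)); noncentrality = dz × √64.

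| True loss | rho | dz | noncentrality | power | non-significant |
|---|---|---|---|---|---|
| half (0.185) | .5 | 0.185 | 1.48 | .308 | 69% |
| half (0.185) | .7 | 0.239 | 1.91 | .469 | 53% |
| total (0.37) | .5 | 0.370 | 2.96 | .830 | 17% |
| total (0.37) | .7 | 0.478 | 3.82 | .964 | 4% |

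**4. The opposite error for secondary hypothesis 2**

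Under the same assumptions, but with no intervention effect and a time drift between pretest and follow-up, the one-arm before-after test is significant with these probabilities (rho .5 to .7), against a nominal .05:
- drift 0.1 SD: .12 to .17
- drift 0.2 SD: .35 to .53
- drift 0.3 SD: .66 to .86

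The drift values are illustrative. The article gives nothing from which to size one.

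**The case against.** The absence of a 6-month control visit belongs to the chosen waiting-list design. The maintenance clauses state that they concern the intervention group, so they make no between-arm claim. This stands as an explanation of the design and means the clauses are not misdescribed. It does not change what they can show, and it does not help secondary hypothesis 2, whose wording is comparative.

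The Personal Determinants sentence can be read as each wave that a given group undergoes. That reading is possible, and Study Design is explicit about the visits, so a clarifying phrase would do. It does not cover the sample-size inputs. The study-flow figure could not be checked here.

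Four stronger readings are tempting, and the document does not support them:

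- *The primary comparison is compromised.* It is not. The pre-to-posttest contrast has data in both arms, stays randomised, and can be estimated even though the control follow-up cell is empty. Only a between-arm contrast at follow-up is lost.
- *Season is fully confounded with durability.* Participants start at different times, and testing runs from January 2018 to July 2019 (Results), so calendar month varies across participants at each wave. The maintenance clauses also span about 4.5 months (6 months less about 6 weeks), not half a year. Season is one possible contributor, of unknown size.
- *The authors will declare maintenance from a non-significant paired test.* Nothing says so. The Statistical Analysis section names multilevel analyses, and the criterion may sit in an analysis plan that is not shown. The figures in step 3 of the working show what such an inference would be worth; they are not a forecast of what will be reported.
- *Attrition makes the figures much worse.* The article expects high dropout but gives no rate, so any smaller analysed number would have no source.

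**Conclusion.** The point holds for the follow-up parts of the hypotheses and no further. Secondary hypothesis 2 is the clearest defect: no randomised contrast can test it over its stated period, although the same outcomes are measured in both arms at posttest. The maintenance clauses of primary hypotheses 1 and 2 and secondary hypothesis 3 can be described but not tested against controls. The limitations in the Discussion do not mention this.

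These conclusions follow from the visit schedule and the wording of the hypotheses and need no numerical assumption. The percentages for undetected loss do. The most fragile assumption is reading 0.37 as an SD difference, since the stated N is matched exactly with 0.37 as f, while a two-group comparison of means with a standardised difference of 0.37, 2:1 allocation and 90% power would need 348. The illustration supports one statement: with at most 64 people, a non-significant change would be weak evidence against a half loss, and would give reasonable evidence against total loss only if the correlation is at the higher end.

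**What to change.** 1. Restate secondary hypothesis 2 as a difference between arms in change from pretest to posttest, using the weight, waist circumference and PROMIS data already scheduled in both arms.
2. Confine confirmatory claims to the pre-to-posttest contrast between arms.
3. Label the 6-month results uncontrolled and descriptive. Report change from baseline and change from posttest, each with a 95% confidence interval, and state that maintenance will not be inferred from a non-significant change. Apply this to both primary hypotheses and to secondary hypothesis 3.
4. Reconcile the sample-size inputs (two groups, three measurements) and the Personal Determinants sentence with the visit schedule in Study Design, and add the missing control follow-up to the limitations.

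No extra visits or measurements are needed. The cost is a weaker durability claim, and secondary hypothesis 2 is tested over about 6 weeks rather than 6 months, a short period for outcomes such as weight and waist circumference to change.

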**Figure 1 figure1:**
[figure not shown]
Study flow.

### Hypotheses

Our primary hypotheses for this study are as follows: (1) The intervention group allocated to the module “Physical Activity” will show an increase in total physical activity from pre- to posttest compared to no change in the control group. This effect will be sustained in the intervention group from the posttest to the follow-up test. (2) The intervention group allocated to the module “Sedentary Behaviour” will show a decrease in sedentary behavior from pre- to posttest compared to no change in the control group. This effect will be sustained in the intervention group from the posttest to the follow-up test.

Our secondary hypotheses are as follows: (1) Positive changes in physical activity or sedentary behavior will be mediated by increases in the personal determinants self-efficacy, action planning, and coping planning. (2) The intervention group will have more positive health outcomes (ie, a lower weight; smaller waist circumference; and lower levels of fatigue, anxiety, and depression) from pre to follow-up test. (3) The negative effect of daily stressors (ie, fatigue, stress, depressed mood, pain, nausea, and feelings of numbness or tingling in limbs) on physical activity and sedentary behavior will be smaller in the intervention group from pre- to posttest compared to no change in the control group. This effect will be sustained in the intervention group from posttest to follow-up test.

As moderation analyses for online interventions targeting adults with type 2 diabetes are not usually performed [5], no hypotheses regarding the moderation effects are made. The following factors will be examined as potential moderators: age, sex, education, and chosen behavior (ie, physical activity or sedentary behavior).

### Participants

The required sample size was calculated using the software GPower 3.1.9.2 [20]. This program requires the following input: effect size, alpha, power, number of groups, and number of measurements. To our knowledge, there is no meta-analysis documenting the effect sizes of online interventions targeting physical activity or sedentary behavior in adults with type 2 diabetes. As people with type 2 diabetes tend to be overweight and physically inactive, we decided to focus on these characteristics for our effect-size estimation [21]. A meta-analysis by Davies et al (2012) showed that eHealth interventions targeting physical activity levels of overweight or sedentary adults reached effect sizes of 0.37 [22]. Most of the studies included in the meta-analysis used questionnaires rather than accelerometers to measure participants’ level of physical activity. Assuming an effect size of 0.37, alpha of .05, beta of .90, two groups (intervention group and control group), and three measurements (pretest, posttest, and follow-up test), the *a priori* power analysis suggests a sample size of 96 (64 participants in the intervention group and 32 in the control group).

Therefore, 96 participants with type 2 diabetes will be recruited via the Ghent University Hospital, the Sint-Lucas General Hospital (Ghent), the Maria Middelares General Hospital (Ghent), and the Damiaan General Hospital (Ostend). To be eligible for participation, participants should have type 2 diabetes, have been diagnosed for at least 1 month, be 18 years or older, speak Dutch, be computer literate, have internet access, and not have participated in previous studies on “MyPlan 2.0.” Participants receiving concomitant care and interventions will not be excluded. Potential participants with type 2 diabetes will be recruited via the endocrinologists of the collaborating hospitals. The endocrinologists will check whether visiting patients meet the inclusion criteria, provide eligible patients with a flyer, and ask these patients if the researchers are allowed to contact them. If the patient agrees, the researchers will receive the patient’s contact details. The recruitment procedures will continue until the proposed number of participants is reached. Except during the pretest, neither the participants nor the researchers assessing the outcome variables will be blinded.

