This study design has several limitations. First, as the resources for this study are limited, we will not be able to collect a large sample size. Consequently, it might be more difficult to identify statistically significant intervention effects. This issue highlights the importance of preventing dropout from the intervention. Dropout will be prevented by sending reminders to participants who are not logging in for follow-up sessions on the website via emails and phone calls. Second, considering the important role of creating a feeling of “goal-ownership” in self-regulation theory, participants can freely choose between the components increasing physical activity and decreasing sedentary behavior. We can therefore not ensure that the two components will have the same number of users. As a result, it might be more difficult to detect an effect for sedentary behavior if a large group selects physical activity as their target behavior and vice versa. As the structure of the intervention and the implemented behavior change techniques are exactly the same for both target behaviors, we decided to perform the analysis with one, rather than two, intervention groups. However, the selected behavior will be added as a moderator to the analysis. Third, in order to test our hypotheses, participants will need to fill out many questionnaires. This might cause higher levels of attrition. Fourth, participants are called weekly by the researchers to check for hypoglycemia or alterations in medication and to assess participants’ personal determinants for change via an interview. Due to these weekly phone calls, participants might show higher levels of engagement with the intervention than they normally would. However, as we will also implement these weekly calls in the control group, we believe that the calls will have a limited impact on the intervention effects. Finally, as the researcher who will analyze the data will also be involved in the data-collection process, blinding of the data analyst is not possible. To account for this issue, a strict protocol has been developed for processing and analyzing the data.

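### The stated power of .90 belongs to one pooled comparison of all 96 participants, not to either module-specific primary hypothesis, and the protocol does not settle which of these is primary

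*Protocol article*

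**What the plan says.** **Sample size (Methods, Participants).** There is a single calculation: "Assuming an effect size of 0.37, alpha of .05, beta of .90, two groups (intervention group and control group), and three measurements". The beta of .90 can only sensibly be read as power. The result is "power analysis suggests a sample size of 96 (64 participants in the intervention group and 32 in the control group"). The effect comes from a meta-analysis in which "eHealth interventions targeting physical activity levels of overweight or sedentary adults reached effect sizes of 0.37".

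**Primary hypotheses (Methods, Hypotheses).** There are two, each tied to one module. First: "The intervention group allocated to the module “Physical Activity” will show an increase in total physical activity from pre- to posttest compared to no change" among controls. Second, the intervention participants in the sedentary behavior module "will show a decrease in sedentary behavior from pre- to posttest compared to no change in the control group". Only the intervention side is limited by module. The control group is not limited by choice.

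**Design (Methods, Study Design).** Participants state their preferred behavior at the first home visit. They are then randomized to the "waiting list control group or the intervention group in a 1:2 allocation ratio", independently of that choice.

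**Analysis (Discussion, Study Implications).** Users of both modules will be analysed as a single intervention arm, with the chosen behavior as a moderator. The authors write: "We can therefore not ensure that the two components will have the same number of users". They add that an uneven split could make one behavior's effect harder to detect. No power per module is given.

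**The concern.** The modules are mutually exclusive and self-chosen, so the 64 intervention participants cannot all count toward each primary hypothesis. A power computed on all 96 is therefore not the power of either hypothesis as worded. The pooled analysis does use all 96, but it does not test those two hypotheses as worded. The module-specific effects would have to come from the chosen-behavior moderator, and Hypotheses says that no moderation hypotheses are made. So Hypotheses and Study Implications disagree on what the primary comparison is, and the .90 fits only one of them.

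The stake is interpretation. A non-significant result for the less popular module could be taken as evidence that it does not work, because the trial is described as having .90 power. In addition, 0.37 is a physical activity effect, so the sedentary behavior hypothesis has no sourced effect size at all.

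**Working it through.** **Inputs.** From Participants: effect 0.37, alpha .05, power .90, 2 groups, 3 measurements, 64 + 32 = 96. From Study Design: 1:2 allocation, with the choice made before randomization in both arms. The split between modules is not given, so every split below is an assumption. No dropout is allowed for.

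**Step 1: reproduce 96.** Take the group-by-time test of a repeated-measures MANOVA, with 0.37 entered as f(V):

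- df1 = (2 − 1)(3 − 1) = 2; df2 = N − 3; noncentrality λ = 0.37² × N.
- N = 96: λ = 0.1369 × 96 = 13.14, power .902.
- N = 95: λ = 13.01, power .898.

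So 96 is exactly the smallest N that reaches .90. Other readings with two groups and three measurements miss it. For example, the repeated-measures ANOVA options with f = 0.37 and correlation .5 need 54 (between groups) or 18 (interaction). The interaction with f = 0.185 comes close (94) only at a correlation of .25, which the protocol does not state. A one-way comparison of three groups has the same arithmetic and also gives 96, but the plan states two groups.

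**Step 2: one module at a time.** Two control groups are possible.

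(a) *Controls who chose the same behavior.* The 2:1 ratio is kept, so λ = 0.1369 × N.

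(b) *All 32 controls*, as Hypotheses literally reads. Either use N alone (λ = 0.1369 × N), or carry the allocation into the noncentrality: λ = c × n1·n2/(n1 + n2). The constant c is set so that 64 + 32 returns 13.14: 64 × 32/96 = 21.33, and c = 13.14/21.33 = 0.616. For 32 + 32, λ = 0.616 × 16 = 9.86. For 13 + 32, λ = 0.616 × 9.24 = 5.70.

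| Share choosing the module (assumed) | (a) n | (a) power | (b) n | (b) by N alone | (b) with allocation |
|---|---|---|---|---|---|
| 80% | 51 + 26 | .820 | 51 + 32 | .851 | .874 |
| 70% | 45 + 22 | .758 | 45 + 32 | .820 | .855 |
| 50% | 32 + 16 | .595 | 32 + 32 | .737 | .789 |
| 30% | 19 + 10 | .373 | 19 + 32 | .625 | .649 |
| 20% | 13 + 6 | .241 | 13 + 32 | .564 | .529 |

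Every entry is below .90, even for a module chosen by four in five.

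**Step 3: the pooled analysis.** It has power .90 for a given outcome if 0.37 holds across all 64. Hypotheses expects each effect only in that module's users. Suppose half the arm targeted the other behavior and showed no effect on this outcome (an assumption). The pooled effect is then 0.5 × 0.37 = 0.185, λ = 0.185² × 96 = 3.29, and power is .34. If the pooled effect were 75% of 0.37, that is 0.2775, λ = 7.39 and power is .67.

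**The case against.** The strongest reply is that the protocol plans a pooled analysis, that the inputs "two groups (intervention group and control group), and three measurements (pretest, posttest, and follow-up test") describe that analysis, and that .90 is the correct output for it. This stands: the calculation contains no arithmetic error. But it does not make .90 the power of the hypotheses that the protocol calls primary, and it depends on the spillover condition in step 3.

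A reader might infer that each hypothesis simply has power .60 at an even split, or .24 for a module chosen by one in five, and that the 96 participants are used up twice over. The documents do not support this as it stands. Those figures need the controls to be limited by choice as well, and Hypotheses does not say so. On its literal wording the 32 controls are shared, and the one-in-five figure more than doubles, to .53-.56. The choice-matched comparison is possible because both arms choose before randomization. It is also the contrast that randomization protects, so both readings belong in the range.

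The authors also disclose the problem in part. Study Implications says that the sample is not large and that an uneven split could hide one module's effect. Participants is open that 0.37 comes from physical activity interventions. Both points stand and lower the severity. What is missing is a number, a corrected statement of what .90 refers to, and agreement between the two sections.

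**Conclusion.** The point holds in this form: .90 is the power of one comparison of all 64 intervention participants with all 32 controls, and it applies to neither primary hypothesis as worded. Module-specific power is about .60 to .79 at an even split and about .24 to .56 for a module chosen by one in five. The lower ends assume choice-matched controls and the upper ends assume all 32. The pooled comparison itself falls to .34 for an outcome if half the arm shows no effect on it.

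All of this takes 0.37 at face value as f(V), uses three measurements as planned, ignores dropout and rests on assumed splits. The underlying defect is that Hypotheses and Study Implications disagree on the primary comparison. The severity is moderate. The total of 96 is not shown to be wrong for the pooled comparison, and the authors already acknowledge the difficulty in words.

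**What to change.** 1. Reconcile Hypotheses with Study Implications: state whether the primary comparison is pooled or module-specific. If it is module-specific, state whether the controls are all 32 or only those who chose the same behavior.
2. In Participants, state that .90 refers to the pooled comparison only and that it assumes the same effect on the outcome in participants who targeted the other behavior. Print power where beta now stands.
3. Add the power of each module-specific hypothesis at 50:50, 70:30 and 80:20 splits under both control-arm readings, labelled as assumed splits.
4. State that 0.37 comes from physical activity interventions and that no sourced effect supports the sedentary behavior hypothesis.
5. Commit to reporting a non-significant module result with its confidence interval, not as evidence of no effect.

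The cost is wording only. The stated power becomes less favourable, and no participants are added.
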